#### Intervention uptake and engagement

 ≥ 80% of patients recruited logging in to the intervention.

#### Completion and follow-up rate

 ≥ 70% of those accessing the intervention providing data at 6-months follow-up.

These criteria aim to retain a sufficient sample size to determine acceptability and feasibility.

#### Primary outcome measures

In line with NIHR guidance on feasibility studies, the focus will be to estimate important parameters that are needed to inform the design of a subsequent larger evaluation, if appropriate. Table 3 details the feasibility study parameters.

**Table 3 Tab3:** Feasibility study parameters

Parameter	Method of assessment
Recruitment rate	The number of eligible patients invited, who provide informed consent to participate in the study, versus those who decline, with reason(s) recorded
Intervention uptake, engagement and adherence	The number of patients who login to access VITALISE The mean and median number of times VITALISE is accessed over the 6-month time period
Completion and follow-up rate	The number of patients who complete the intervention, baseline and follow-up assessment outcome measures. Reasons for loss to follow-up will also be recorded

We will collect demographic data (age, sex, ethnicity, socio-economic status) on patients who decline to take part and record reasons for declining/unsuitability to inform the way in which the programme is promoted in the future.

Acceptability of VITALISE will be assessed qualitatively using in-depth, semi-structured interviews and all patients recruited will be invited to take part. Topics will focus on patients’ perceived expectations, benefits, motivations, and barriers to using/accessing VITALISE. These topics will be explored in relation to age and liver disease severity. We will qualitatively assess fidelity of receipt and enactment of the intervention to provide an indication of whether participants used the intervention as intended to make behavioural changes. Our interview topic guide will contain specific questions about each component of the intervention to determine whether they were received by participants and whether they utilised each component as intended. This information will inform optimisation of the intervention ahead of a large-scale evaluation, if appropriate. Those who drop out of the intervention will be invited to interview to explore reasons for drop-out. Findings will inform intervention optimisation.

We will also collect data on the number of patients who log in to the intervention, the number of times they access each module, attend coaching appointments, and the length of coaching calls, to enable us to provide context around study outcomes – i.e., is it likely that any preliminary changes observed are a consequence of engagement with the intervention.

### Secondary outcome measures

Body weight, height, waist and hip circumference, blood pressure, blood tests (glucose, lipid profile, LBTs, FBC, HbA1c), liver stiffness measurement and calculation of clinical scores (QRISK^3^, FIB-4, NFS) will be measured as part of standard care.

#### Physical activity

Physical activity will be objectively measured using an ActiGraph GT9X accelerometer worn on the non-dominant wrist for a minimum of 8 h per day over seven consecutive days during the first and last week of the intervention. Daily total activity counts, steps, time spent sedentary, and time spent in light, moderate, and vigorous activity will be recorded. Freedson thresholds based on metabolic equivalents will be used to demarcate to intensity of physical activity: sedentary (≤ 100 counts/min), light (101–1951 counts/min), moderate (1952–5724 counts/min), and vigorous activity (≥ 5725 counts/min) [23, 24]. Self-reported physical activity will be assessed with the Godin Leisure-Time Exercise Questionnaire using the total leisure activity score [20] at baseline, 12-weeks and 6-months.

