### Patient identification and consent process

Patients will be recruited from the Liver Unit at NuTH. Eligible patients will be given/sent a study invitation letter and participation information sheet. At the clinic visit, the treating physician will discuss the study with eligible patients following receipt of standard NHS care (i.e. review, examination, and blood tests). If the patient is interested in taking part, a research team member will provide them with more information about the study, answer any questions, obtain written informed consent, collect baseline data, and offer an induction to the intervention (either on the same day as the clinic appointment, or on an alternative day if preferred by the patient).

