### Preparation procedures

A member of the research team will use a study-specific medical questionnaire to collect sociodemographic and clinical data including information on medical history and current medications (See supplementary file). Body weight, height, waist and hip circumference, blood pressure, blood tests (glucose, lipid profile, liver blood tests [LBTs], full blood count [FBC], HbA1c), liver stiffness measurement [LSM] by Fibroscan and calculation of clinical scores (QRISK^3^, Fibrosis-4 (FIB-4) Score, NAFLD Fibrosis Score (NFS)) will be measured as part of standard care. Patients with Type 2 diabetes (T2DM) will be monitored as part of standard care and medications adjusted in response to weight loss/dietary change/physical activity as necessary. This will be reported as part of the evaluation.

Patients will be asked to complete a physical activity questionnaire (the Godin leisure-time physical activity questionnaire [20]) and Patient Activation Measure (PAM) [21] as part of the research study at baseline, 12-weeks and 6-month follow-up. Patients will also be given an accelerometer to wear for 7-days (to objectively measure physical activity levels) which will be returned to the research team in a pre-paid envelope at baseline and 6-month follow-up.

VITALISE has been developed in collaboration with a commercial organisation, ‘Changing Health Limited’, who are a leading provider of lifestyle behaviour change programmes to the NHS (Changing Health | Digital Behaviour Change At Scale). Changing Health provide evidence-based education and lifestyle coaching digital solutions for people with type 2 diabetes across the UK and renders its innovative services customised to their clients’ requirements. With the patient’s permission, the research team will send their email address, and full name to Changing Health who will subsequently email the patient a welcome email allowing them to access the VITALISE intervention and setup their profile. A researcher will provide patients with a demonstration of how to login to VITALISE. Table 1 outlines the summary schedule of investigations.

**Table 1 Tab1:** Summary schedule of investigations: (* = completed as part of standard care). Patients will be asked to self-report their weight, physical activity levels and complete the PAM at 12-weeks. This interim “visit” will be conducted by telephone

Visit	1	2 (Virtual)	3
**Timescale**	**0**	**12-weeks**	**6-months**

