### Intervention

Patients will be given a personal login for VITALISE and will have continuous access for a 6-month period prior to their follow-up appointment with a hepatologist. They will be supported by monthly personalised tele-coaching sessions delivered by specifically trained lifestyle coaches. A pedometer will be provided to allow patients to record daily step count. Table 2 provides and overview of VITALISE content.

**Table 2 Tab2:** Overview of VITALISE content: to be added into page 9 under table 2 heading

Module	Sub-components	Description of information content
**Module 1: Introduction**	**Welcome to VITALISE with Changing Health**	Message from a specialist in lifestyle management of NAFLD providing an overview of the aims and objectives of the programme
**Module 2: Understanding non-alcoholic fatty liver disease (NAFLD)**	**What is NAFLD?**	Overview of the liver; what is NAFLD and how it progresses; the different stages of the disease
	**How is NAFLD diagnosed?**	Overview of the tests/investigations that may be used to diagnose NAFLD
	**Understanding your health results**	What the different tests/investigations measure and what the results mean
	**NAFLD myths**	Common myths about NAFLD and why it shouldn’t be left unmanaged
	**Managing your NAFLD**	Animations demonstrating how lifestyle change can improve liver health, reduce cardiovascular disease risk and improve metabolic control
	**Patient success stories**	Real-life examples of how people with NAFLD or at risk of NAFLD have improved their liver health by making lifestyle changes
	**Long term heath complications from NAFLD**	Potential consequences of not managing NAFLD
**Module 3: Getting started with coaching**		How to access lifestyle coaches and what to expect from coaching sessions
**Module 4: Food and NAFLD**	**Energy balance**	How to balance energy requirements in the context of weight loss
	**Nutrition and NAFLD**	The relationship between diet quality, eating patterns and NAFLD
	**Understanding carbohydrates**	What are carbohydrates and the role they play in our diet
	**Understanding fats**	What are fats and the role they play in our diet
	**Understanding alcohol**	Recommended alcohol intake; calorie content in alcoholic drinks; provision of an online alcohol calculator
**Module 5: How do I make changes to my diet?**	**Finding the right dietary approach**	Animation explaining the evidence supporting two dietary approaches for managing NAFLD

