#### Patient activation/empowerment

Patients will be asked to complete Patient Activation Measure (PAM) [21] at baseline, 12-weeks and 6-months. The PAM questionnaire collects data on an individual’s knowledge, skills and confidence to manage their health and is a global measure of an individual’s overall ability to manage their health.

Questionnaires will be given to patients in the clinic to take home and return by post in pre-paid envelopes alongside their accelerometer. We will look at return rates for questionnaires/accelerometers as part of the feasibility study and address issues/seek patient feedback on ways to improve this for the larger scale evaluation as necessary.

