### Data and statistical analysis

#### Quantitative analysis

The flow of participants throughout the trial will be reported in a Consolidated Standards of Reporting Trials (CONSORT) flowchart. Reasons for declining to take part in and for withdrawing from the study will also be recorded in the CONSORT flowchart. Descriptive statistics will be used to present baseline characteristics and feasibility outcomes. A paired t-test or Wilcoxon signed-rank test (depending on data distribution) will be used to evaluate changes in outcomes from pre- to post-intervention, with the mean difference and 95% confidence interval presented.

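### The baseline accelerometer week is placed inside the intervention, so the pre- to post-intervention change in measured activity starts from an on-intervention value

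*Protocol article*

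**What the plan says.** All references are to the Protocol article.

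- **Wear windows.** The Physical activity section has the ActiGraph worn "over seven consecutive days during the first and last week of the intervention".
- **Label.** Preparation procedures describes the same device as one "which will be returned to the research team in a pre-paid envelope at baseline and 6-month follow-up". Table 1 puts 7-day accelerometry at visit 1 (time 0) and visit 3 (6 months).
- **Order at the clinic.** Under Patient identification and consent process, the research team will "obtain written informed consent, collect baseline data, and offer an induction to the intervention". The induction may be "either on the same day as the clinic appointment, or on an alternative day if preferred by the patient".
- **Questionnaires.** PAM and Godin are scheduled for baseline, 12 weeks and 6 months. Patient activation/empowerment adds: "Questionnaires will be given to patients in the clinic to take home and return by post in pre-paid envelopes alongside their accelerometer".
- **Access.** Under Intervention, patients "will have continuous access for a 6-month period prior to their follow-up appointment with a hepatologist".
- **Analysis.** Quantitative analysis uses a paired t-test or Wilcoxon signed-rank test "to evaluate changes in outcomes from pre- to post-intervention", with a mean difference and 95% confidence interval.

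**The concern.** The contrast to be analysed needs a first measurement that the intervention has not touched. For accelerometry, the only section that dates the wear week puts it in the first week of the intervention. Steps and activity are what VITALISE tries to change: Module 8 contains goal-setting and step-tracking tools, a pedometer is supplied, and email prompts are weekly for the first four weeks. Any response in that week is counted as baseline. With one arm, the patient's own first value is the only comparator, so nothing else in the design offsets the error, and it cannot be undone at analysis.

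The stake is limited but real. Aims and objectives makes testing the robustness of the data collection procedures a primary objective, and asks as a secondary objective whether participation leads to changes in physical activity and patient activation. The Discussion says that the outcome data will inform the likely size and variability of effects for a larger evaluation.

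**Working it through.** The plan gives no figure on this point, so there is none to reproduce. The check sets the sections side by side and then shows how an early response would carry through.

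**1. Baseline accelerometry.** Physical activity places the wear in the first week of the intervention. Preparation procedures and Table 1 call it baseline, and Quantitative analysis treats the first value as pre-intervention. These cannot all be literally true. Listing baseline data before induction does not resolve it: seven days of wear cannot be finished before an induction held the same day.

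**2. Outcomes affected.** Six kinds of accelerometer output are listed: total counts, steps, sedentary time, and light, moderate and vigorous time. Weight, bloods, blood pressure and Fibroscan are standard-care measures and are not affected.

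**3. PAM and Godin.** Both are labelled baseline. The forms go home and come back with the accelerometer, and no section requires completion before login. Late completion is therefore possible, but it is not stated.

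**4. Follow-up wear.** One section says the last week of the intervention; others say the 6-month follow-up. Access runs for six months before that appointment, so last-week wear ending just before the visit would satisfy both. A device handed out at visit 3 would instead be worn after the access period. The text does not say which is meant.

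**5. Illustration (f is an assumption, not in the documents).** Let D be the true change and f the share of D already present in week 1. Then:

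- observed change = (1 − f) × D
- if a later paired study is sized on the observed change with the same SD, the required number of patients is multiplied by 1/(1 − f)²

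| f | Share of D observed | If D = 0.5 SD | Multiplier on n |
|---|---|---|---|
| 0 | 100% | 0.50 SD | 1.0 |
| 10% | 90% | 0.45 SD | 1.23 |
| 25% | 75% | 0.375 SD | 1.78 |
| 50% | 50% | 0.25 SD | 4.0 |

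If activity rises early and then fades below its week-1 level but stays above the true baseline (f > 1), the observed change takes the opposite sign.

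**6. Scale against random error.** At exactly the 80% uptake and 70% follow-up criteria, 35 × 0.8 × 0.7 = 19.6, about 20 patients with 6-month data. The half-width of the 95% interval for a paired mean change is t(0.975, n − 1)/√n. This is 0.47 SD of the change for n = 20 and 0.34 SD for n = 35. With D = 0.5 SD, the shift is 0.5 − 0.375 = 0.125 SD at f = 25%, and 0.5 − 0.25 = 0.25 SD at f = 50%. Both are smaller than the half-width. Unlike random error, though, the shift would not shrink with more patients.

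**The case against.** The strongest reply is that only the baseline accelerometer wording is at fault, and that it matters little. Much of this stands.

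- **PAM and Godin.** A reader might infer that these too are measured after the intervention starts. The documents do not say so: both are labelled baseline, and baseline data are listed before induction. Taking forms home permits late completion but does not plan it.
- **Exposure in week 1.** Induction may be on another day, the welcome email follows only after details are passed to the provider, and the pedometer and first coaching call are not dated. How much exposure falls in the wear week is therefore unknown. This does not remove the contradiction, because the Physical activity section itself counts that week as part of the intervention.
- **Follow-up.** A reader might infer that the second wear takes place after the intervention. That requires the device to be handed out at visit 3, which no section states. The sentence about handing out in clinic has the questionnaires as its subject, and dispatch details may sit in the full protocol. What stands is only that two descriptions are used where one would do.
- **Importance.** The study is not powered and excludes formal hypothesis testing. None of the criteria for progressing uses a change in activity or PAM. This limits the severity.
- **Remedy.** Moving the questionnaires into the clinic would remove the baseline postal return, whose return rates the study sets out to examine. The remedy should therefore keep it.

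**Conclusion.** The point holds for baseline accelerometry. Followed as written, the plan measures change in the accelerometer outcomes from a week inside the intervention while calling it pre-intervention. For PAM and Godin there is a gap: the forms may be completed after access starts. For the follow-up wear there is an unclear window, not a demonstrated clash.

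Underestimation is the likely direction, on the assumption that part of the response appears early and persists. It is not established: an early rise that fades could reverse the sign, and the documents give no figure for the size. The 10% to 50% range above is illustrative only.

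Severity is moderate to minor. These are secondary outcomes in a small feasibility study and no progression criterion depends on them. The point is still worth correcting, because the estimates are intended to inform the size and variability of effects in the larger evaluation, and the order of measurement cannot be repaired afterwards.

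**What to change.** 1. Have the baseline accelerometer worn for its seven days, and the take-home PAM and Godin forms completed, before the welcome email is triggered and the pedometer is issued. Keep the postal return as planned.
2. Record wear dates and form completion dates against the date of first login, so that any overlap can be seen and reported.
3. State one follow-up wear window, for example the last week of access, ending before the 6-month visit. Use it in Preparation procedures, Table 1 and Physical activity alike.

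If access cannot be held back, the minimum is to call the first wear period week 1 of the intervention and to stop describing the resulting change as pre- to post-intervention. That makes the description correct but leaves the bias in place.

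Cost: about one week between consent and access, with a possible small effect on the uptake criterion, and possibly one posted pack before the 6-month visit. No new measurements are needed.

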## Aims and objectives

The aim of the study is to evaluate the feasibility and acceptability of VITALISE in the clinical setting within secondary care. This feasibility study will not include formal hypothesis testing because it is not powered to detect clinically meaningful changes in outcomes. The main aim is to gain insight into whether patients find VITALISE acceptable and whether it is feasible to deliver within routine clinical care.

In accordance with NIHR and CONSORT guidance for feasibility studies [16, 17], the primary objectives are to determine recruitment, retention and attrition rates, intervention uptake, engagement, adherence, and follow-up rates and to test the robustness of our data collection procedures. We will collect data on usability and individual patient views on VITALISE via semi-structured interviews to add important context to quantitative outcome data. Importantly, we will look at the demographics of patients who participate versus those who decline. We will seek information from those who decline to explore ways in which these barriers to participation can be overcome.

The secondary objective is to determine whether participation in the intervention leads to changes in outcomes including physical activity, diet, body weight, HbA1c, liver enzymes, liver stiffness, blood pressure, lipid profile (all measured as part of standard care using the NAFLD Care Bundle) [18] and patient activation/empowerment. These preliminary data will provide some indication of whether the intervention could be effective as part of routine clinical care.

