### Sample size

With reference to best practice guidelines on sample size requirements for feasibility studies [19] and practical time frames, we will aim to recruit 35 patients over a 6-month time period.

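### Counts from a wrist-worn accelerometer are scored with Freedson intensity bands and no stated wrist calibration, so time in each band may be misclassified (minor, secondary outcome)

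*Protocol article*

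**What the plan says.** The Physical activity section of the Protocol article, under Secondary outcome measures, fixes four things.

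- **Device and site:** an "ActiGraph GT9X accelerometer worn on the non-dominant wrist".
- **Wear:** "for a minimum of 8 h per day over seven consecutive days during the first and last week of the intervention".
- **Output:** "Daily total activity counts, steps, time spent sedentary, and time spent in light, moderate, and vigorous activity will be recorded".
- **Scoring:** "Freedson thresholds based on metabolic equivalents will be used to demarcate to intensity of physical activity", with the bands "sedentary (≤ 100 counts/min), light (101–1951 counts/min), moderate (1952–5724 counts/min), and vigorous activity (≥ 5725 counts/min". Two references are cited for the thresholds. Neither a wrist calibration nor a conversion is stated, and no sensitivity analysis is named.

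Under Quantitative analysis, a paired t-test or a signed-rank test "will be used to evaluate changes in outcomes from pre- to post-intervention, with the mean difference and 95% confidence interval presented". The Discussion says that the outcome data will inform how large effects may be, and how variable, when a larger evaluation is designed.

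**The concern.** A counts-per-minute cut-point links device output to energy cost at the site where the two were compared. The arm moves in many tasks in which the trunk hardly moves, so the same minute can give different counts at the wrist and at the waist. If bands made for one site are applied to the other, minutes fall into the wrong category.

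The article writes down both the site and the numeric bands, so this is a stated scoring rule and not a detail left for later. At stake is the only objective measure of physical activity, which is the first outcome named in the secondary objective. Distorted minutes, and distorted variability of their change, would pass into the planning of the next study.

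A smaller related matter is wear time. Only a minimum daily wear is set, and the comparison is before and after in one arm. If daily totals were analysed as they stand, a change in wear between the two weeks could not be separated from a change in behaviour.

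**Working it through.** **Inputs from the document:** bounds 100, 1952 and 5725 counts/min; non-dominant wrist; minimum wear 8 h per day; paired comparison of two weeks.

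**Assumptions, not in the document:** the bands were calibrated at the waist or hip; wrist counts are *k* times the counts there, with *k* from 1.5 to 4. For the minutes below, also 14 h of wear and lognormal counts per minute with 60% of minutes in the sedentary band and 3% at or above the moderate bound when *k* = 1.

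**Step 1, the bands themselves.** 100 + 1 = 101, 1951 + 1 = 1952 and 5724 + 1 = 5725. They are contiguous, so there is no internal error in the numbers.

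**Step 2, effective bounds.** A bound *T* applied to wrist counts acts as *T*/*k* on the calibration scale. For example, 1952/1.5 = 1301 and 1952/4 = 488.

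**Step 3, illustrative minutes.** The two percentages fix the lognormal: SD = (ln 1951.5 − ln 100.5)/(1.881 − 0.253) = 1.82 and mean = ln 100.5 − 0.253 × 1.82 = 4.15. Minutes per day are the share in each band × 14 × 60.

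| *k* | 100 acts as | 1952 acts as | 5725 acts as | Sedentary min | Moderate + vigorous min |
|---|---|---|---|---|---|
| 1 | 100 | 1952 | 5725 | 504.0 | 25.2 |
| 1.5 | 67 | 1301 | 3817 | 430.3 | 40.8 |
| 2 | 50 | 976 | 2862 | 377.6 | 56.1 |
| 3 | 33 | 651 | 1908 | 305.2 | 84.5 |
| 4 | 25 | 488 | 1431 | 257.0 | 110.3 |

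Moderate-plus-vigorous time is 1.6 times (40.8/25.2) to 4.4 times (110.3/25.2) its value at *k* = 1. These figures show direction and sensitivity only. They are not estimates for this trial.

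**Step 4, what remains in the before-after change.** Suppose every count rises 1.5-fold by 6 months, a deliberately large change.

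- At *k* = 1, moderate-plus-vigorous time moves from the first table row to the second: 40.8 − 25.2 = +15.6 min.
- At *k* = 2, it moves from the *k* = 2 row to the *k* = 3 row: 84.5 − 56.1 = +28.4 min.
- The error in level at *k* = 2 is 56.1 − 25.2 = 30.9 min. The error in the change is 28.4 − 15.6 = 12.8 min.
- For sedentary time the two changes are 430.3 − 504.0 = −73.7 and 305.2 − 377.6 = −72.4 min, almost the same.

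In this example the change carries less of the bias than the level does, but some remains for moderate and vigorous time.

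**Step 5, wear time.** Minutes in a band = share of wear time × hours worn × 60. With an unchanged 60% sedentary share, 8 h gives 0.6 × 480 = 288 min and 14 h gives 0.6 × 840 = 504 min. Wear of 8 h in the first week and 12 h in the last would raise every unscaled total by 12/8 − 1 = 50%. As a percentage of wear time the change is zero. The document does not suggest that wear would differ in this way.

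**The case against.** The strongest objection is that the calibration site is nowhere in the document and the two cited sources cannot be seen. That is true, and it is why the waist or hip origin stands here as an assumption and the size is left open. It does not remove the point. That cut-points are specific to a body site is general measurement knowledge, and the article pairs a wrist device with named bands and gives no support for that pairing.

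A second objection is that the outcome is secondary and that the Aims state "This feasibility study will not include formal hypothesis testing because it is not powered to detect clinically meaningful changes in outcomes". The same device, site and bands are also used at both times, total counts and steps do not depend on the bands, and a separate activity questionnaire is collected. All of this stands and limits the weight of the point. It does not make the minutes in each band valid.

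Third, a reader might infer that daily totals will be analysed without regard to wear time. The document does not say so. It lists what is recorded and is silent on scaling, non-wear detection and valid days, which a condensed article may leave to the full protocol or SAP. The 8 h figure may also be an instruction to patients and not a validity rule. Only a request for confirmation follows from this.

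**Conclusion.** The article applies Freedson bands to wrist counts without a stated wrist calibration, and this should be changed or justified. If the bands come from the waist or hip and wrist counts run higher, moderate and vigorous time is overstated and sedentary time understated. The direction rests on those two assumptions. The size is unknown: for an assumed ratio of 1.5 to 4, the 1952 bound acts like 1301 to 488.

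Two stronger readings are not supported. One is that the intensity results will be wrong by a known amount; the document gives no conversion factor. The other is that the feasibility conclusions are undermined. None of the criteria for recruitment, uptake or follow-up uses accelerometer data, and the return rate of devices does not depend on how they are scored. This is a minor point about a secondary outcome. It is still worth acting on, because the outcome data are meant to inform the later evaluation.

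**What to change.** Score the recorded data with cut-points validated for the non-dominant wrist and cite that validation. Alternatively, drop the intensity bands and report total counts and steps. In either case, express the accelerometer outcomes per wear-hour or as a percentage of wear time, unless the full protocol or SAP already does so.

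The cost is low. Rescoring needs no further patient contact, provided that the epoch or raw files are kept, which the article does not state. The downside is less direct comparability with reports that use the Freedson bands. Moving the device to another body site would be a change to data collection and not a rescoring, so it is not part of this proposal.
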